**Treatment Assignment Procedures**

Randomization allocation sequence will be concealed from the participant enrollment team and will be maintained in the soft copy by the Principal Investigator, who will implement the randomization in a separate room in microbiology laboratory, and will discard the urine samples of the control arm.

No previous records will be shared with the blinded outcome assessors, who will be provided blank printed formats with only the identification details of the participants. No one will be authorized to break the blinding.

**9.3 Definition of Populations**

Intention to treat analysis will be considered when all the participants complete the study protocol and there is no loss to follow up. Per protocol population will be considered when any of the participant will not be able to complete the antibiotic regimen.

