**8. INTERVENTION DISCONTINUATION**

The criteria for discontinuing the intervention for a participant:

1. If the participant experiences any adverse event due to an antibiotic prescribed, the participant can discontinue the regimen prescribed and seek medical help.

2. If the participant decides to no more be a part of the study and refuses to provide the information related to the outcome of pregnancy

The criteria for discontinuation of the intervention of rapid test:

1. If more than 10% participants report that the antibiotics prescribed based on the results of the rapid test could not arrest the disease process or turn symptomatic (although the rapid test has been validated in multicentric studies previously)

Even if the participants discontinue antibiotic regimen, they will be followed up for the outcomes of the pregnancy. Participants need to report any signs and symptoms of UTI if they discontinue the antibiotic regimen.

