**9.2 Sample Size and Randomization**

Sample size was calculated based on type 1 error of 5%, power of 80%, global rate of preterm birth as 10.6% and that of low-birth-weight as 14.6%, combined rate of preterm or low-birth-weight (primary outcome measure) extrapolated as 25%. Based on the contribution of asymptomatic bacteriuria to total preterm birth and low-birth-weight, which varies from 6.9% to 20.5%24, the expected incidence of preterm birth or low-birth-weight in intervention arm for sample size calculation, was safely assumed to be 15% lower than the above-extrapolated global incidence of 25% in the control arm, as a minimally important difference for success of the experiment. Loss to follow up was accounted for 10% participants (5% in each arm). The sample size calculation estimated 120 participants to be enrolled in each arm, with a total 240 participants to be enrolled in the study.

Intention-to-treat analysis will be done in the original groups in which the participants are allocated. Incidence of other maternal and perinatal events will be described as frequencies. In case there is loss to follow up, complete case analysis will be done. In case there is any protocol deviation, per protocol analysis will be done.

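### Sections 9.2 and 9.3 conflict on when intention-to-treat applies, name no primary analysis set, and leave room for a per-protocol exclusion that can bias the comparison

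*Protocol*

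**What the plan says.** Section 9.3 (Definition of Populations) has two sentences. The first is "Intention to treat analysis will be considered when all the participants complete the study protocol and there is no loss to follow up". The second is "Per protocol population will be considered when any of the participant will not be able to complete the antibiotic regimen".

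Section 9.2 (Sample Size and Randomization) states without condition that the analysis will be by intention-to-treat in the groups as allocated. It then names complete case analysis for loss to follow-up, and adds: "In case there is any protocol deviation, per protocol analysis will be done".

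Section 8 (Intervention Discontinuation) says: "Even if the participants discontinue antibiotic regimen, they will be followed up for the outcomes of the pregnancy".

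Three other places matter. The Précis says that usual care includes no urine culture and no antibiotics for asymptomatic bacteriuria. Section 3 says that control urine samples are discarded. Section 5.1 says that the rapid test is run on intervention-arm samples.

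**The concern.** Intention-to-treat exists to deal with women who do not complete the protocol. A rule that applies it only when everyone completes defeats that purpose. Section 9.2 gives a different rule, so the protocol does not settle which women enter the primary comparison.

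The 9.3 trigger for per-protocol is an event after randomisation, and for the course started at screening that event can occur in one arm only. A woman can be a non-completer of that course only if she was tested, found positive and treated. Her counterpart in the control arm is never identified and cannot be excluded. If non-completers are dropped, the arms are no longer comparable, and the protocol's own premise (sections 2.1 and 2.2) is that bacteriuria raises the risk of preterm birth and low birth weight.

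The choice of set should also not be left open, because the Principal Investigator holds the allocation sequence (section 9.2), enters the rapid test results (10.1), reviews deviations (10.3.4) and analyses the outcomes (9.5).

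**Working it through.** **The plan's own sample size.** Section 9.2 gives 5% type I error, 80% power, 25% events in the control arm and a reduction of 15%, read here as absolute (25% against 10%).
- Two-sided, uncorrected: n = [1.96·√(2·0.175·0.825) + 0.842·√(0.25·0.75 + 0.10·0.90)]² / 0.15² ≈ 100 per arm.
- With continuity correction: 113 per arm. Then 113/0.95 ≈ 119, close to the stated 120.

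The 120 per arm is thus reproduced. The point below does not depend on how it was derived.

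**Can the 9.3 condition be met?** The protocol allows for 10% loss, described as 5% in each arm. With independent losses among 240 women:
- at 5%: 0.95^240 ≈ 4.5 × 10⁻⁶;
- at 10%: 0.90^240 ≈ 1.0 × 10⁻¹¹.

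These figures concern loss only. They show that the 9.3 condition for intention-to-treat will fail. They do not show a move to per-protocol, because for loss section 9.2 names complete case analysis.

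**How many women could the 9.3 exclusion remove?** Section 2.1 gives a prevalence of 1.9% to 9.5%. If the test finds exactly the bacteriuric women (assumed), expected positives are 120 × 0.019 = 2.3 to 120 × 0.095 = 11.4. The protocol gives no non-completion rate; 20% and 50% are assumed here. The chance of at least one non-completer is 1 − (1 − prevalence × non-completion)^120. At 20% non-completion this is 37% at the low prevalence and 90% at the high one. At 50% it is 68% and 99.7%.

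**What would their removal do with no true effect?** Let both arms have a 25% event rate, let f = prevalence × non-completion, and let r be the event risk in the removed women (assumed). The remaining intervention rate is q = (0.25 − f·r)/(1 − f), and the false difference is 0.25 − q.

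| Prevalence | Non-completion | Women removed | r | q | False difference (points) | Type I error |
|---|---|---|---|---|---|---|
| 1.9% | 50% | 1.1 | 50% | 24.8% | 0.2 | 5.0% |
| 1.9% | 50% | 1.1 | 100% | 24.3% | 0.7 | 5.2% |
| 9.5% | 20% | 2.3 | 50% | 24.5% | 0.5 | 5.1% |
| 9.5% | 20% | 2.3 | 100% | 23.5% | 1.5 | 5.8% |
| 9.5% | 50% | 5.7 | 50% | 23.8% | 1.2 | 5.6% |
| 9.5% | 50% | 5.7 | 100% | 21.3% | 3.7 | 10.3% |
| any | any | – | 25% | 25.0% | 0 | 5.0% |

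Example (sixth row): f = 0.095 × 0.5 = 0.0475, so q = (0.25 − 0.0475)/0.9525 = 0.2126 and the difference is 0.0374. Type I error is for the uncorrected two-sided test by normal approximation, with 120 controls against the women left in the intervention arm.

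**The case against.** Four points can be made for the plan, and each limits what may be concluded.

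1. A reader might infer that a single lost woman moves the analysis to per-protocol. The documents do not say that. For loss, section 9.2 names complete case analysis, and complete cases in their allocated arms are close to what a sound plan would use. Per-protocol is tied to antibiotic non-completion (9.3) or to a deviation (9.2).

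2. Per-protocol may be meant as an additional analysis. Section 9.2 promises intention-to-treat without condition, and 9.3 says only that the per-protocol population will be considered. This reading is possible, but neither section states it, and 9.3 taken literally withdraws intention-to-treat. The ambiguity stands.

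3. A reader might infer that exclusions can fall only on the intervention arm. Section 7 provides repeat testing and antibiotics for later urinary tract infection in both arms, and the deviations described in 10.3.4 (improper evaluation or urine collection) can occur in either. Only the course triggered by screening is one-sided.

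4. The bias may be small or absent. Few women will test positive, and section 5.4 plans telephone follow-up of adherence. The direction rests on the removed women having above-average risk, for which the protocol gives no figure. This is correct, and it is why the point is that the comparison can be biased, not that it will be.

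**Conclusion.** The defect stands as a contradiction between two stated rules, not as a detail left to an analysis plan. Section 9.3 makes intention-to-treat depend on a condition with a chance of about 4.5 × 10⁻⁶ at 5% loss. Section 9.2 says something else, and no primary set is named.

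Under the assumptions above, the resulting bias is at most about 0.7 points at 1.9% prevalence with non-completion up to 50%. At 9.5% prevalence it is 0.5 to 1.5 points with 20% non-completion and 1.2 to 3.7 points with 50%. It favours the intervention if the removed women are at higher risk and is zero if they are at average risk.

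A reader might go further and call the bias as large as the effect under study. Section 9.2 puts the contribution of bacteriuria at 6.9% to 20.5% of a 25% event rate, which is 1.7 to 5.1 points. The 20% scenario lies below that range, and only the 50% scenario overlaps it, so the documents do not support the statement.

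The wording should be corrected before analysis because the rule governs the primary comparison. The size of the bias is not the main reason.

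**What to change.** Rewrite the analysis-set sentences in 9.2 and 9.3 so that they agree:

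- The primary analysis always includes every randomised woman with a known outcome, in the arm to which she was allocated, whatever her antibiotic completion or protocol deviations.
- The per-protocol analysis is labelled supplementary and never replaces the primary one.

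A sensitivity analysis for women with missing outcomes is optional and can be left to the statistical analysis plan.

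The cost is a few sentences of wording. No new data are needed for women who stop antibiotics, since section 8 keeps them in outcome follow-up. The sample size stays at 120 per arm: for 25% against 10%, power by the uncorrected normal approximation is 86.9% with 120 per arm, 85.1% with 114 (5% loss) and 83.1% with 108 (10% loss).

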**9.4 Interim Analyses and Stopping Rules**

No interim analysis is proposed for the trial. The stopping rule will be when more than 10% participants report that the antibiotics prescribed based on the results of the rapid test could not arrest the disease process or turn symptomatic.

**9.5 Outcomes**

Outcomes will be analyzed by the Principal Investigator. The documentation of the outcome will be validated by the Principal Investigator based on the supporting medical records collected.

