Blinding will be done for only the outcome assessors, who will visit the participants after delivery, to collect data related to the outcomes.

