**6.2.4 Followup Visits**

Although study will not require any additional follow up visit to the hospital, but the participants will be encouraged to come for regular antenatal checkups as scheduled by the obstetricians. The routine tests and assessment of antenatal checkups will be carried out as per the guidelines of the institute. In case of any adverse event or urinary tract infection, the participants will be shared contact number of the Principal Investigator and research staff, who will facilitate the care provision at the hospital.

Since the participants need not deliver in Gandhi Hospital itself, or may not necessarily deliver around the Expected Date of Delivery, a follow up visit will be conducted by outcome assessors to the hospital where they will be admit or at home if the delivery is already over. The coordination will be done around EDD on telephone.

The follow up visit should be completed by the outcome assessors around the delivery or as soon as possible. The outcome assessors will collect data on week of gestation at the time of delivery, birth weight, any maternal or perinatal co-morbidity encountered, and will collect the snapshot of the discharge card or treatment record as per the availability with the participant.

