**10. DATA COLLECTION AND QUALITY ASSURANCE**

**10.1 Data Collection Forms**

The research staff enrolling the participants in antenatal clinic will include an MD doctor and a lab technician. The identification details, inclusion/exclusion criteria, clinical history and examination details of signs and symptoms, and antenatal history will be recorded in a prespecified format by the doctor. The result of the rapid test will be entered by the Principal Investigator in the same format in the designated space.

The outcome assessors will be provided a separate format to record the outcomes. They will be provided only the identification details.

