**10.3.5 Monitoring**

Once a week monitoring visit will be made by the Principal Investigator to antenatal clinic. The records and consent forms will be reviewed daily by the Principal Investigator. A sub-sample of 5% of delivered women will be revisited by the Principal Investigator at their home for outcome assessment.

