| **Nausea** | ❑ |  |  |  |
| **Vomiting** | ❑ |  | **H. Outcome of pregnancy** | |
| **Fever** **(>38ºC)** | ❑ |  | **Birth Weight-** | |
| **Costo-vertebral** **angle** **tenderness** | ❑ |  | **Gestational age at delivery-** | |
| **Chills** | ❑ |  | **Any complication/death-** |  |
| ***Asymptomatic*** | |  |  |  |
| **No** **symptoms** | ❑ |  |  |  |

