**Appendix 4 Data Collection Format for Outcome Assessors**

Field Data Collection Checklist

| Date of visit |  |
| --- | --- |
| Enrolment number |  |
| ANC Number |  |
| IPD Number |  |
| Name |  |
| Alias/AKA |  |
| Age |  |
| Husband’s Name |  |
| Education |  |
| Did you sign any telugu form at Gandhi Hospital before pregnancy | □Yes □No  □I Don’t remember |
| Date of Delivery |  |
| Name and address of the hospital where she delivered |  |
| Gender of the baby |  |
| Weight of the baby at birth |  |
| Other outcomes/complications/ death during pregnancy/delivery/ postpartum(baby/mother) |  |
| Documents whose pic is collected | □Discharge card □Indoor ticket □Delivery Note □Baby note  □Other-Specify-______________ |
| Signature of Mother |  |

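### The investigator who holds the allocation list also validates and re-assesses outcomes, and the blinded assessors' form has no field for gestational age at delivery

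*Protocol*

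**What the plan says.** **Who is blinded.** Section 3 limits the blind to one group: "Blinding will be done for only the outcome assessors, who will visit the participants after delivery, to collect data related to the outcomes". Under Treatment Assignment Procedures, these assessors get no previous records and nobody is authorised to break the blinding. Section 9.5.1 has them measure the primary outcome.

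**What the Principal Investigator does.**
- Keeps the allocation sequence and is the person "who will implement the randomization in a separate room in microbiology laboratory, and will discard the urine samples of the control arm" (Treatment Assignment Procedures).
- Records test results: "The result of the rapid test will be entered by the Principal Investigator in the same format in the designated space" (section 10.1).
- Manages the data (section 10.2) and analyses the outcomes (section 9.5).
- Checks the outcomes: "The documentation of the outcome will be validated by the Principal Investigator based on the supporting medical records collected" (section 9.5).
- Re-assesses some of them: "A sub-sample of 5% of delivered women will be revisited by the Principal Investigator at their home for outcome assessment" (section 10.3.5).

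**Where the outcome is written down.** Section 6.2.4 states: "The outcome assessors will collect data on week of gestation at the time of delivery, birth weight". The assessors' form in Appendix 4 has the delivery date and "Weight of the baby at birth", but no entry for gestational age, last menstrual period (LMP) or expected date of delivery (EDD). The entry "Gestational age at delivery" stands in section H of Appendix 3, the enrolment form.

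**The concern.** The primary outcome is a composite of preterm birth, low birth weight, or both. Birth weight is a number read from a record. Preterm status also depends on how the pregnancy was dated, and the protocol leaves room for judgement there. Women may enrol in any trimester, and pregnancy may be confirmed by a urine test without ultrasound (section 4.1). Delivery may take place at another hospital, and records are collected as available (section 6.2.4). Near the preterm threshold, status can turn on which record is accepted.

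If the person checking that record knows the woman's arm and test result, the comparison is exposed to the detection bias that blinded assessment is meant to prevent. The protocol assigns these roles explicitly, so this is not detail left to an analysis plan.

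**Working it through.** **1. Roles side by side.** The person who knows the allocation (Treatment Assignment Procedures) and the test result (section 10.1) is the person who validates (9.5), revisits (10.3.5), manages data (10.2) and analyses (9.5). None of these sections states masking to arm. None says which value stands if the investigator and the assessor differ.

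**2. Text against forms.**
- Week of gestation at delivery: assigned to the assessors in 6.2.4; absent from Appendix 4; present only in Appendix 3, section H.
- Birth weight: assigned to the assessors in 6.2.4; present in Appendix 4, and also in Appendix 3, section H.
- Delivery date: present in Appendix 4.
- Gestational age at enrolment: present in Appendix 3, section F. The assessors do not receive it, so they cannot calculate gestation at delivery from it.
- EDD: used in 6.2.4 to time the follow-up contact, but neither form has a field for it.

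Birth weight is thus first recorded blind and exposed only later, at validation and revisit. Gestational age at delivery has no blinded field at all.

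**3. The protocol's own sample size (section 9.2).** Inputs: 25% against 10% (the absolute reading of 15% lower), 5% type 1 error taken as two-sided, 80% power, 1:1 allocation. With continuity correction this gives 113 per arm. Allowing 5% loss, 113 / 0.95 = 118.9, so 119, which agrees with the stated 120. The present point does not change that figure.

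**4. Effect of one reclassification.** Assume 5% loss in each arm: 120 × 0.95 = 114 evaluable women. One woman moves that arm's rate by 1 / 114 = 0.88 percentage points. The planned 15-point difference corresponds to 0.15 × 114 = 17.1, about 17 women.

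**5. How many recodings give p<0.05 with no true effect.** Assume 28 events in each arm (25% of 114 is 28.5; 28/114 = 24.6%), tested by uncorrected Pearson chi-square.
- 11 intervention-arm events recoded as non-events (17 against 28): p = 0.067.
- 12 recoded (16 against 28): p = 0.044.
- 7 changed in each arm in opposite directions (21 against 35), 14 in all: p = 0.031.

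**6. Reach of the revisit.** 0.05 × 240 = 12 women at most, or 0.05 × 228 = 11.4 if only evaluable women are counted.

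**The case against.** Several stronger readings are tempting, and the document does not support them.

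- *Preterm status can be settled only from the enrolment form.* The assessors photograph the discharge card, delivery note or similar records while blinded, and these may show gestation. Appendix 3 also holds a gestational age taken at enrolment by staff from whom the sequence is concealed; with the delivery date, gestation at delivery could be calculated from it. What is missing is a blinded field, the basis of dating, and a rule requiring that calculation.
- *The investigator decides every outcome.* Section 9.5 speaks of validating documentation against records, which may be no more than source verification. It gives no power to overrule the assessor. The revisit stands under Monitoring, and nothing says it replaces the assessors' data. What remains is that the check is unmasked and that no rule covers disagreement.
- *The blinding does not protect the primary outcome at all.* Birth weight is on the blinded form, and at the protocol's rates it is the larger component (14.6% against 10.6%).
- *A handful of reclassifications would undo the trial.* Applying the protocol's attributable share to its 25% rate gives 0.25 × 0.069 = 1.7 to 0.25 × 0.205 = 5.1 points, which two to six women would match. That benchmark assumes the whole share is removed and is not the difference on which the trial was sized.

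Two further points carry weight. As reproduced, Appendix 3 has no field for randomised arm or test result (its arm box distinguishes asymptomatic from symptomatic), so its link to the test result rests on section 10.1. And the analysis is a single 2×2 Pearson test (section 9.6), so an unmasked analyst has little latitude; unmasked validation is the greater concern.

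**Conclusion.** The point holds in a limited form. The trial's one blind is weakened because outcome documentation is validated, and a sub-sample re-assessed, by the person who holds the allocation and test results, with no masking and no disagreement rule. Section 6.2.4 and Appendix 4 also contradict each other on gestational age at delivery. The exposure is greatest for preterm birth, and smaller for birth weight.

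Under the assumptions of 114 evaluable women per arm and 28 events in each, a few recodings would shift the estimate by about 0.9 points each, but a false significant result would take about 12 in one direction. These figures describe sensitivity; they are not evidence that bias will occur. The matter should be corrected, but it does not invalidate the design.

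**What to change.** 1. In Appendix 4, add gestational age at delivery and the record it was taken from. Remove section H from Appendix 3.
2. In Appendix 3, record the EDD and the basis of dating next to the gestational age already taken, before randomisation. Derive preterm status by formula: gestation at delivery = gestation at enrolment + (delivery date − enrolment date) / 7, or equivalently from the fixed EDD and the delivery date.
3. In sections 9.5 and 10.3.5, assign validation and the 5% revisits to existing staff without access to allocation or test results, for example assessors checking each other's cases. State how disagreements are resolved.
4. State that outcome coding is fixed before it is linked to the allocation list.

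The cost is edits to two forms and some reassignment and training of existing staff, since section 6.2.3 asks only that assessors be graduates with some field experience. The investigator would see outcomes later. One weakness remains: women given antibiotics can infer their arm (section 5.2) and may disclose it to an assessor. Deriving preterm status by formula limits the effect of that on the preterm component.
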